# A study to explore the role of a low threshold, fitness focussed physical rehabilitation intervention with protein supplementation to target physical function and frailty in people with problematic substance use and homelessness: protocol for a single-arm pre-post intervention study.

**DOI:** 10.12688/hrbopenres.13678.2

**Published:** 2024-10-29

**Keywords:** Inclusion health, addiction, homelessness, exercise, nutritional supplementation

## Abstract

**Background:**

People who are homeless are more likely to experience poor mental health and addiction as well as suffering from non-communicable diseases. There is evidence of frailty and accelerated physical ageing among people experiencing homelessness. Appropriate physical rehabilitation and nutritional supplementation strategies can stabilise or reverse frailty and general physical decline, but it is not known how this type of intervention would work in practice in this population.

**Aim:**

To evaluate the feasibility and pre-post intervention impact of a low threshold physical rehabilitation intervention with protein supplementation to target physical functioning and frailty in people with problematic substance use who are experiencing homelessness.

**Methods:**

The intervention will consist of a 12-week low threshold rehabilitation programme with protein supplementation. Participants will be service users of the Ballyfermot Advance Project, a day services centre for people with addiction issues and experiencing homelessness. Primary outcomes will be feasibility including numbers recruited, retention of participants and adherence to the exercise intervention and protein supplement. Any adverse events will be recorded. Secondary outcomes will be strength and muscular mass, physical performance and lower extremity physical function, pain, frailty and nutritional status.

**Discussion:**

An immediate impact may be simply a distraction from difficult circumstances and potentially an improvement of physical health of participants, which can be a conduit for the emergence of other positive behaviours and recovery. Longer term, this study will generate preliminary data on which to inform the design of a definitive randomised controlled trial of physical rehabilitation and protein supplementation, if indicated.

**Ethics and dissemination:**

Ethical approval was granted by the Faculty of Health Sciences Research Ethics Committee in TCD. Study findings will be disseminated through publication into an international peer-reviewed journal and presented at national and international conferences.

## Introduction

Inclusion health is an approach which aims to prevent and address health and social inequalities of vulnerable people such as those who are homeless
^
1
^. The collision of disease risk factors with poverty, constant stressors and social exclusion in people experiencing homelessness has demonstrated a markedly elevated rate of non-communicable diseases
^
2
^. Related to non-communicable diseases and a complex interaction of other factors such as addiction and accidental death, socially excluded populations have a mortality rate that is almost eight times higher than the average for men, and nearly 12 times higher for women
^
3
^. The median age of death among people experiencing homelessness
^
4
^ in Dublin, Ireland is staggeringly low among females at 38 years and 44 years among men
^
5
^.

Accelerated ageing and earlier geriatric conditions such as falls, poor strength and mobility problems are common in people experiencing homelessness
^
6,
7
^. A single centre, cross-sectional study, which applied a broad test battery of physical functioning tests to people experiencing homelessness who were admitted for inpatient care, demonstrated that despite a low median age of 45 years, 83% of participants had mobility problems and 70% were frail or pre-frail
^
5
^.

As frailty, a complex multidimensional state of physiological vulnerability
^
8
^ and pre-frailty, its prodromal stage
^
9
^, is normally a concept associated with ageing
^
10
^ - the concept of frailty in younger populations can be contentious. Nonetheless, frailty has been identified in younger populations across a number of settings
^
11,
12
^ and it is recognised that those living in areas of greater deprivation experience the earlier onset of illness and associated disability
^
13,
14
^. A high prevalence of frailty has been identified in people experiencing homelessness
^
6,
15–
20
^. Poorer physical health and frailty means people experiencing homelessness have fewer options for moving to independent housing due to accessibility issues which reinforces the cycle of entrenched homelessness, rough sleeping and dependence on long-term hostel accommodation
^
21
^. The challenge is to bridge the implementation gap and provide innovative solutions to key challenges faced by people in long term homelessness. Improvements in physical health will not solve all complex challenges, it is nonetheless a sensible solution focussed target which can be a positive focus from which there can be a ripple effect in terms of outcomes.

Key drivers of physical frailty are poor nutritional intake
^
22
^ and sedentary behaviour. Food insecurity is extremely prevalent among people experiencing homelessness
^
23
^ and may contribute to frailty. It is possible that protein supplementation after exercise may optimise protein synthesis rates
^
24
^ and help stabilise frailty and physical de-conditioning
^
25
^. This has been successfully demonstrated in frail older people
^
26
^. Furthermore, in illicit drug users, exercise can increase the abstinence rate and can reduce withdrawal and anxiety symptoms
^
27
^.

There is a dearth of research exploring physical activity and nutritional interventions in this population. Kendzor
*et al.*, 2017 investigated the effects of a diet and exercise intervention in homeless adults
^
28
^, in a randomised controlled trial. This study, however, did not provide a structured, supervised exercise programme. The intervention involved the provision of educational newsletters, healthy snacks and pedometers with advice on physical activity. This study is the first of its kind which will provide a structured exercise and nutritional intervention in this population.

## Aim and objectives

The overall aim of this study is to test the feasibility and pre-post intervention impact of a low threshold physical rehabilitation programme with dietary supplementation to target frailty and poor physical functioning in people who are homeless.

Objectives:

1.To evaluate recruitment, retention and adherence to the physical rehabilitation and protein supplementation programme.2.To examine baseline and pre-post intervention change in measures of physical, nutritional and frailty status, and self-reported pain.3.To ascertain perceptions of unmet physical health needs, exercise habits and how an exercise intervention should ideally be designed to meet the needs of this cohort with lived experience of homelessness and active addiction issues.

## Methods

### Design and study setting

This single arm feasibility study is taking place in a surburban area od Dublin with high levels of deprivation. The study will commence in October 2022 and will finish in March 2023. The Ballyfermot Advance Project provides a five-day a week meal service, as well as drug and alcohol related services for people with active addiction issues, the majority of whom experience homelessness. A dedicated exercise room in a nearby community centre has been allocated for the duration of the intervention period. This study has received ethical approval from the Faculty of Health Sciences REC at Trinity College Dublin (Ethical Approval Reference Number: 211202.

### Obtaining consent

All potential participants will be provided with a PIL and an exercise information leaflet detailing the purpose of the data collection, the exercise intervention, potential risks and benefits and data protection rights. Due to the expected high levels of functional illiteracy, the research physiotherapist will read the study related information where applicable and will be available to answer any study related queries. Where possible there will be a seven-day gap between receipt of the PIL and obtaining consent to allow potential participations time to consider participation. Due to the anticipated fluctuation in interest levels however, and other competing priorities related to mood, motivation and active addiction issues, flexibility has been built into the consent process. This means that clients who express an interest in the programme and willingness to participate the same day as first receiving the study information can be consented and commence the programme at a time suited to them. This method was successfully employed previously in a cross-sectional study conducted with patients experiencing homelessness in St. James’s Hospital
^
6
^.

Once the research physiotherapist is satisfied that the potential participant has read (or has been read to) and fully understands the PIL, they will proceed to obtain written informed consent. Obtaining consent will take place at the first interaction with the participant prior to commencement of testing. The written consent informs participants that they are permitted to withdraw from the study at any time. Participants are given their own copy of this consent form and PIL, signed by themselves and the research physiotherapist. The research physiotherapist will be accompanied by a second research assistant.

### Inclusion and exclusion criteria

The aim of the study is to be as pragmatic and low threshold as possible. This means that minimal constraints are put in place to access the intervention. In order to be as pragmatic as possible in terms of inclusion criteria, all clients (>18 years) accessing services in Ballyfermot Advance who consent to study participation can be included in this study. Only participants with problematic behavioural issues, including confusion or extreme agitation, or have major physical problems, (medical or orthopaedic) which would preclude ability to safely participate in the exercise class will be excluded from study participation. Participants with a confirmed pregnancy will also be excluded as physical functioning/performance tests scores in advanced stages of pregnancy may vary from baseline values
^
29
^.

In the design of this study, we were cognisant of the likely complex needs of many participants as complex childhood trauma has been commonly experienced by people who experience homelessness and substance misuse problems. Using a Trauma Informed approach to care
^
30
^ and based on experience from a previous Inclusion Health undergraduate clinical placement
^
31
^, the following were incorporated in the approach to assessment and follow up with participants; (i) empathy, (ii) consistency, (iii) understanding, and (iv) flexibility.

### Intervention

The intervention will consist of three exercise opportunities, including a twice weekly, 12-week exercise programme with nutritional supplementation. The intervention will be fully supervised and delivered by two research physiotherapists. Group exercise classes or one-to one sessions will be delivered depending on participant preference. Participants will be advised of a schedule of class times, including gender specific classes and will be allocated to a specific class based on their preference. An alternate class will be offered if participants cannot attend at their scheduled time. A ‘Park Walk’ will also be scheduled one day per week. This will be a 30-minute self-paced walk of low intensity led by the research assistant involved in this programme. This is to build up exercise frequency during the week and is building in a habit which it is hoped can be continued by participants beyond the life cycle of the project. Flexibility in programme commencement and completion dates will be provided to enable the 12-week intervention to be completed within a 15-week period of time.

The PAR-Q
^
32
^, a pre-screening questionnaire, will be conducted with participants prior to commencement of the exercise classes. The research physiotherapist will, with permission, write to the participants General Practitioner (GP) to advise them of their intention to take part in the programme and to clarify that it is safe for them to proceed with the exercise intervention. If the individual does not have a GP, the research physiotherapist will discuss this individual case with a specialist consultant in Inclusion Health based in St. James’s Hospital, Dublin. The case will be outlined in broad terms, without revealing any personal details of the participant, solely as a sounding board as to whether it would be suitable for the participant to attend or not.

The exercise intervention will focus on general fitness and will include resistance, aerobic and functional exercises, with in-built flexibility based on individual participants’ needs. The exercise component will be based on ‘core’ exercises (
Table 1) which will be adjusted to increase or decrease difficulty based on the results of the initial assessment and ability of participants, as judged by the research physiotherapist. Each session, of approximately 20 minutes duration, will commence with a warm-up and stretch of the major muscles and will end with cool-down and stretch.

**Table 1. T1:** Exercise Circuit.

Core exercise	Initial Intensity	Progression/Adaptations*
Sit to stand/squats/lunges	2 sets 10–15 reps	3 sets of 15 reps use of weights/ball
Elbow Bends	2 sets 10–15 reps	3 sets of 15 reps weights
Step-ups	2 sets 10–15 reps	3 sets of 15 reps height of step; weights
Arm elevations	2 sets 10–15 reps	3 sets of 15 reps weights
‘Penguin waddle’-hip abduction	2 sets 10–15 reps	3 sets of 15 reps With additional upper limb abduction and elevation; movement with 360° turns
Scapular retractions	2 sets 10–15 reps	3 sets of 15 reps weights
Aerobic activity	2 mins	3 mins ladders, hurdles, skipping ropes, jumping jacks dance, game with cones/balls
Balance	4–5 mins	5 mins Tandem; single leg stance, upper limb and trunk movements; weights and ball work

Adaptations: exercises individualised and progressed for each participant by research physiotherapist

A low-specification pedometer will be supplied to encourage increasing daily step count and goal setting will be discussed with participants. This is to build a scientifically sound psychological framework into the intervention to encourage motivation to partake in physical activity.

The intensity of the workout will be managed by using the Borg Perceived Rate of Exertion (RPE) scale
^
33
^ where participants will be advised to exercise at a rate of between 11 and 13 on the PRE scale, i.e. where they find the exercise somewhere between ‘fairly light’ to ‘somewhat hard’, where they find it hard to have a conversation but can comfortably continue to exercise.

To promote post-exercise muscle protein synthesis
^
24
^, a nutritional supplement (200ml pre-prepared ‘protein shake’ Fresubin,
https://www.fresubin.com/) which consists of 20g of protein will be offered to all participants immediately post exercise in the exercise room.

In an attempt to build sustainability beyond the life cycle of the project, participants will also be educated about exercise and available local resources where possible. Participants will be invited and encouraged to return three times weekly to continue with the exercise intervention.

### Adherence

The service provided will be low threshold to facilitate adherence and compliance. The research physiotherapists will make every effort to be flexible and accommodating to participants in terms of their attendances to the exercise classes and the Park Walk. Adherence to the programme will be measured by the uptake, compliance and number of repeat visits to the drop-in programme. Demographic information will include biological sex and current homeless status.

### Demographic details collected

Demographic details, including age, and named GP of participants will be collected. A letter will be sent to each GP to inform them of study participation. Questions around current addiction status will be guided by Section 1 of the Treatment Outcome Profile
^
27
^. As the research physiotherapist will not have access to participant medical/social records, senior staff of Ballyfermot Advance Project will provide pertinent medical/addiction/social information relating to the participants if required.

### Recruitment and retention

The numbers recruited and frequency of attendances will be recorded. Participants will be encouraged to attend all sessions if possible. Drop out will also be recorded.

### Adherence

The research physiotherapists will make every effort to be flexible and accommodating to participants in terms of their attendances and adherence to the programme. Adherence will be measured by the adherence to the exercise programme and the protein supplement.

e recorded. The service provided will be low threshold to facilitate its feasibility

### Secondary outcomes

**1. Strength and muscular mass:** Muscular strength will be estimated
^
34,
35
^ by using a Digital Hand Dynamometer in a sitting position while the hand is unsupported with the elbow at 90° flexion and the underarm and wrist in neutral. Two measurements will be inputted as part of the SHARE-FI frailty instrument
^
36
^ and values will also be compared to normative reference values established by Steiber
^
37
^.

Mid-calf circumference girth will be evaluated as this measure correlates with appendicular muscular mass
^
38
^. This will be measured using a flexible tape measure at the level of the largest circumference of the calf. Higher scores indicate higher levels of muscular mass. The cut-off value for moderately and severely low calf circumference is 34 cm and 32 cm in males, and 33 cm and 31 cm in females
^
39
^.

Mid-arm muscle circumference reflects both muscle mass and caloric and protein adequacy, and may be used to signify malnutrition or wasting
^
40
^. This test has been recommended for use in physical testing of those experiencing homelessness
^
41
^ due to the high prevalence of lower limb swelling
^
42
^. The maximum upper arm muscular mass will be measured using a flexible tape measure. Results will be compared to global reference values
^
43
^.

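### Calf girth is read as muscle mass where leg swelling is said to be common, and a tape-only arm girth is labelled muscle circumference, so fluid or fat change may be misread as muscle change

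*Protocol article*

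**What the plan says.** The abstract lists strength and muscular mass first among the secondary outcomes ("Secondary outcomes will be strength and muscular mass, physical performance and lower extremity physical function, pain, frailty and nutritional status"). Item 1 of Secondary outcomes assigns two girths to that heading.

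- **Calf.** The reason given is "Mid-calf circumference girth will be evaluated as this measure correlates with appendicular muscular mass". The method is "This will be measured using a flexible tape measure at the level of the largest circumference of the calf", and the direction of scoring is "Higher scores indicate higher levels of muscular mass". Two thresholds per sex follow, for moderately and for severely low girth: 34 and 32 cm for men, 33 and 31 cm for women. No condition for swelling is attached.
- **Arm.** The stated meaning is "Mid-arm muscle circumference reflects both muscle mass and caloric and protein adequacy, and may be used to signify malnutrition or wasting". The test is said to be recommended in people experiencing homelessness "due to the high prevalence of lower limb swelling". The method is "The maximum upper arm muscular mass will be measured using a flexible tape measure", and results are compared with global reference values.

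The Analytic plan compares initial and final values with paired t-tests or the Wilcoxon signed-rank test. The Discussion confirms that there is no comparator group.

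**The concern.** The text undercuts its own calf measure. Leg swelling is a reason to prefer an arm measure only if swelling compromises measurement of the leg. Yet the calf is still read as muscle and set against cut-offs, without asking whether the leg is swollen. At baseline, swelling enlarges the calf and can hide low muscle mass. Over the 12 weeks, falling swelling can look like muscle loss or mask a gain, and rising swelling can look like a gain.

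The arm measure was brought in with swelling in mind but has a separate fault: the name promises muscle, while the tape records the whole limb. A rise may be fat.

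Muscular mass is a named secondary outcome. The Intervention section gives the protein supplement in order to promote muscle protein synthesis after exercise. The results are also meant to inform the design of a randomised trial, so a mislabelled outcome could be carried into it.

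**Working it through.** The article states no figure for measurement error, swelling or fat change, so there is nothing of the plan's own to reproduce. The check sets the statements side by side and then uses simple geometry for scale.

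**Step 1. Inputs from the documents (Secondary outcomes, item 1).**
- Calf cut-offs, moderately / severely low: men 34 / 32 cm, women 33 / 31 cm.
- Gap between cut-offs: 34 − 32 = 2 cm in men; 33 − 31 = 2 cm in women.
- Leg swelling: described as highly prevalent, with no percentage, size or expected change.
- Instrument for both girths: flexible tape. No skinfold or other fat correction appears anywhere in the article.

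**Step 2. What each tape reading contains.**
- Calf girth depends on muscle, bone, fat and any fluid. The scoring sentence treats it as muscle alone.
- Arm girth depends on muscle, bone and fat. To approximate muscle circumference, the fat layer must be removed: muscle circumference = girth − π × skinfold. Even that still includes bone. With no skinfold, what is recorded is total girth.

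**Step 3. Scale for the calf (assumed layer thickness, muscle held constant).** Treat the calf as a circle. A uniform layer of thickness t adds 2πt to the girth.

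| Assumed layer t | Added calf girth (2πt) |
|---|---|
| 1 mm | 0.63 cm |
| 2 mm | 1.26 cm |
| 3 mm | 1.88 cm |
| 5 mm | 3.14 cm |

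A layer that spans the full 2 cm between cut-offs has t = 20 mm / 2π ≈ 3.2 mm.

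Not everyone changes category. With a 1 mm layer, a man is lifted to the upper cut-off only if his unswollen girth lies between 34 − 0.63 = 33.37 cm and 34 cm. With a 3 mm layer the band runs from 34 − 1.88 = 32.12 cm to 34 cm.

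**Step 4. Scale for the arm (assumed skinfold S, muscle held constant).** Total girth exceeds muscle circumference by πS: 1.57 cm at S = 5 mm, 3.14 cm at 10 mm, 4.71 cm at 15 mm, 6.28 cm at 20 mm and 7.85 cm at 25 mm. A skinfold change of 1 to 5 mm between visits moves girth by 0.31 to 1.57 cm.

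**Step 5. What the design can separate.** The observed change in each girth is the muscle part plus the fluid or fat part. Only the sum is measured. A paired test on the sum cannot split it, and there is no control group whose fluid or fat change could be subtracted. The sign of the error is not fixed.

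**The case against.** The strongest reply has four parts.

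- **Swelling is recognised.** An upper-limb measure is included with that problem in view. This deserves credit, but it does not repair the calf reading, which remains scored and set against cut-offs.
- **The wording is softer in places.** The calf is said to correlate with muscle, and the arm is said to reflect calorie and protein adequacy as well. That is fair. It leaves the unconditional scoring sentence and the arm outcome's name as they are.
- **A condensed article omits measurement detail.** A swelling check or skinfold step may exist elsewhere, and the article refers reliability and validity to Extended data that are not shown. Still, the point rests on what is stated: an unconditional reading, a tape and a name that the tape cannot deliver.
- **The consequence is limited.** The primary outcomes are recruitment, retention and adherence, and grip strength, chair stand, nutritional score and BMI give context. This stands.

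Three stronger readings are tempting, and the documents do not support them.

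- A reader might infer that fluid or fat change will be reported as muscle. No section says how a change in girth will be worded, and whether such changes occur is unknown.
- A reader might take the 2 cm gap as the size of the error. It is only the distance between two thresholds; the layer thicknesses above are assumed, and a small shift moves only people near a cut-off. The Analytic plan does not say that category shifts will be analysed.
- A reader might conclude that the arm reference values are the wrong ones. Whether they are for total or muscle circumference cannot be told from the documents.

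**Conclusion.** The point holds as one of interpretation and labelling. As written, calf girth is equated with muscle in a population said to have much leg swelling, and total arm girth carries the name of a muscle measure. Any fluid or fat change between visits may be misread as muscle change, upwards or downwards, and the uncontrolled design cannot tell them apart.

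The size is unknown. The geometry assumes a circular limb, a uniform layer and constant muscle. It shows only that changes of a few millimetres would not be negligible beside the plan's cut-offs. The primary feasibility outcomes are untouched. The change is worth making because it is cheap and because these data are intended to shape a later trial.

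**What to change.** **Calf.** Record lower-limb swelling (yes/no) at both visits. Report girth and its change for all participants with swelling flagged, and add a sensitivity summary in those without swelling at baseline. Do not read girth or its cut-offs as muscle mass where swelling is present. Defining the subset at baseline is deliberate. Requiring no swelling at either visit would select on a state measured after the intervention, which exercise might alter, and would further shrink a sample already limited to completers. Swelling that appears later is then handled by the flag.

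**Arm.** Rename the outcome mid-upper-arm circumference, confirm that the reference values are for that same measure, and interpret change beside change in BMI rather than as muscle mass.

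**Cost.** One tick-box per visit, some rewording, and fewer calf values that can be read as muscle mass. BMI needs no new data. The stated collection window was October 2022 to March 2023. If collection is over and swelling was not noted, the flag and the sensitivity summary are lost. The arm label, the reference check and removal of the unconditional calf reading can still be done in the report.
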